## Abstract

**Introduction:**

Chronic pain is a common health condition that significantly impacts the quality of life of those affected, affecting one in five people in Canada. The prevalence of this condition tends to increase with age, making it a major health issue given the ageing population. However, its management remains inadequate and requires significant mobilisation of healthcare professionals as well as the development of multiple therapeutic solutions. Among these, non-pharmacological interventions such as hypnosis and virtual reality have proven effective. Nevertheless, while the existing literature seems promising, it presents methodological limitations. Therefore, this study aims to assess the effectiveness of an intervention combining virtual reality and hypnosis in an ageing population suffering from a widespread chronic pain condition, that is, hand arthritis.

**Methods and analysis:**

This study will be a single-centre randomised clinical trial. Participants will be randomly assigned to one of two conditions: one receiving an intervention combining virtual reality and hypnosis, and the other receiving only virtual reality. The effectiveness of the intervention on current perceived pain before and after the intervention (primary outcome) will be evaluated. Secondary outcomes will include anxiety and depressive symptoms, quality of life, relaxation and fatigue. Exploratory analyses will also be conducted to contribute to the emerging literature by examining physiological variables such as heart rate variability, respiratory rate and electrodermal activity during the intervention, and their relationship with primary and secondary outcomes.

**Ethics and dissemination:**

The project was approved by the Research Ethical Committee of the Hospital Maisonneuve-Rosemont (Project no 2024-3539). Participants will be asked to provide written consent for their participation. Results from this study will be shared through peer-reviewed publications, as well as oral and poster presentations at scientific events. The protocol for this study was preregistered on Open Science Framework and raw anonymised data will be available on this platform (https://osf.io/vbh72/?view_only=1d17c5708f894faab6669d85e1fde75d).

**Trial registration number:**

NCT06833905.

STRENGTHS AND LIMITATIONS OF THIS STUDYThis study considers both subjective and objective evaluations of chronic pain.The intervention is developed following a solid methodological framework.A risk for a floor effect should be considered, given the modalities of this study.This study will pave the way for a randomised controlled trial.

## Introduction

 Recognised as a distinct condition in the 11th edition of the International Classification of Diseases (ICD-11),^1 2^ chronic pain can be defined as an unpleasant sensory and emotional experience associated with or resembling that associated with actual or potential tissue injury.^3^ Thus, chronic pain is a subjective experience that can persist for more than 3 months and can be influenced by biological, psychological and social factors.^3 4^ Chronic pain has been reported to affect approximately one in five individuals in Canada, representing an estimated 8 million people.^5^ Considering that the proportion of individuals affected by chronic pain increases with age^6 7^ and that Canada is following a population ageing trend, it is expected that the prevalence of chronic pain and its repercussions on society will increase significantly. Projections indicate that by 2030, an additional million Canadians will be affected.^5^ Among the most common conditions leading to chronic pain in the elderly, arthritis-related conditions are prevalent.^7^

Chronic pain’s effects on psychological and physical health greatly influence a person’s quality of life. According to reports, 36% of individuals with chronic pain state that the pain is bothersome and prevents them from completing certain daily activities, thereby affecting their family and community.^8^ Because chronic pain impedes autonomy and independence, the elderly consider their pain as a top concern in their daily life.^9^ Furthermore, due to its persistent nature, chronic pain can lead to depressive and anxiety symptoms, insomnia, social isolation and may contribute to the development of mental health disorders and substance use.^5 8^

### Chronic pain management

Prolonged waiting times in public healthcare establishments for treatment of chronic pain, which can sometimes exceed 4 years,^10 11^ encourage opioids to be used as a conventional treatment because of their time-efficiency and high effectiveness for reducing pain.^12 13^ However, since the use of opioids as a treatment is, among other factors, associated with an increased risk of overdose, substance abuse and heart attacks,^14^ it is crucial to find non-pharmacological solutions to treat chronic pain and help reduce the negative outcomes of the opioid crisis in Canada.

Many non-pharmacological treatments claim to be efficient in reducing chronic pain, including meditation, clinical hypnosis and more recently, virtual reality.^15 16^ Clinical hypnosis is defined as a state of focused attention and reduced peripheral awareness resulting in an increased ability to respond to suggestions.^17^ Studies show that clinical hypnosis is an effective treatment for all four components of chronic pain, while also improving quality of life and reducing anxiodepressive symptoms and perceived pain.^18^ Virtual reality is the intentional simulation of experiences presented to the individual’s senses.^15^ This more recent intervention is also considered an effective treatment for reducing chronic pain^19^,^21^ and anxiodepressive symptoms.^22 23^ Virtual reality does so by diverting attention away from the pain experienced by individuals.^24^ Regarding the most promising type of virtual intervention, virtual nature exposure seems to be a fruitful avenue. Indeed, the effects of nature exposure are well documented, allowing for lower psychological stress and increased mood.^25^,^28^ Those effects appear to be dose-dependent, as they are maximised when people are exposed for >30 minutes/week.^29^ Given the physical limitations of patients, it appears useful to develop tailored means to bring nature to patients and virtual reality is one of them. In that sense, studies have explored the effects of virtual exposure to nature which appear to be similar to real nature exposure,^30^,^32^ demonstrating that virtual reality is a suitable solution. Considering that virtual reality and hypnosis (VRH) seem to have common mechanisms in pain management, by targeting focused and peripheral attention, combining both treatments could be an interesting approach to explore their added value in enhancing pain relief and improving patient outcomes.

### Virtual reality hypnosis

Combining VRH could increase the number of individuals who can benefit from this treatment, as this combination would address the limitations of hypnosis (ie, availability of qualified therapists, time and effort required from therapists for each patient, and patients’ ability to exert the cognitive effort needed to engage in hypnosis).^33^ The addition of virtual reality would notably reduce the cognitive effort required to generate visual stimuli associated with hypnotic suggestions, decrease the need for constant guidance from a specialised professional, eliminate the necessity of visiting a healthcare facility to receive treatment and standardise the variability in hypnotic techniques used by different practitioners.^33 34^ Therefore, a VRH intervention in pain treatment could be defined as hypnotic inductions and analgesic suggestions delivered through a personalised virtual reality software.^35^

Few studies have evaluated the effects of VRH in patients suffering from chronic pain, most of them being case studies or restricted to small samples, but results reveal positive outcomes.^36^,^38^ In a case study featuring a woman suffering from neuropathic pain, which prevented her from going outside or wearing certain clothing items, only VRH significantly improved her quality of life by reducing both the intensity and duration of her pain, compared with other ineffective treatments such as meditation, acupuncture and regular hypnosis.^36^ Other studies show that VRH not only helps reduce pain perceived by patients, but also reduces their anxiety levels.^39^ Although current studies evaluating the effectiveness of VRH as a treatment to reduce pain showcase promising results, there are only a few. They also have certain methodological limitations, including small sample sizes, no control group and are mostly focused on acute pain. Thus, to promote new non-pharmacological treatments for chronic pain, the efficacy of VRH in reducing pain perception must be evaluated by following a more rigorous methodology. Moreover, to bring comparable data on the efficacy of such an intervention on chronic pain symptoms, measurements should be comparable with those used in studies on acute pain. In that sense, considering that pain is a subjective experience of objective stimuli,^40^ physiological measures could be used to detect pain perception, as well as other indicators of quality of life-related variables.^41 42^ Most common physiological measures of pain perception are respiratory rate, heart rate, heart rate variability and electrodermal activity.^43^,^45^ Although the literature is not unanimous and mostly focused on acute pain, studies suggest that an increase in respiratory rate, heart rate and electrodermal activity, as well as a decrease in heart rate variability, is associated with higher levels of pain perception.^46^,^48^

### Objectives

The main objective of the present study is to evaluate the effectiveness of a VRH intervention in reducing pain experience in patients with chronic pain. Given the prevalence of chronic pain in the ageing population and that arthritis-related pain is among the most common conditions leading to those symptoms, this population was chosen to test the intervention. This will be achieved by comparing an experimental group, receiving the VRH treatment, to an active control group. It is expected that the subjective and physiological pain scores of individuals who received the intervention will indicate lower levels of pain than those who did not receive the intervention. It is also expected that pain scores of individuals who received the VRH intervention will show a significant reduction in pain perception between the first and last treatment session, with this effect remaining stable over time (ie, 3 weeks after the final session).

A secondary exploratory objective is to observe the impact of VRH treatment on quality of life and anxiety-depressive symptomatology. Exploratory objectives are to explore the effects of the intervention on physiological activity and on medication consumption.

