### Measures

#### Primary outcome

The different dimensions of perceived pain levels will be measured using the Brief Pain Inventory–Short Form (BPI-SF).^52 53^ The BPI-SF is a self-administered nine-item questionnaire used to assess the impact of pain on patients' daily functioning. Participants are asked to rate the intensity of their worst, least, average and current pain on scales from 0 to 10, list ongoing treatments and their perceived effectiveness, and indicate the extent to which pain interferes with their usual activities. This questionnaire covers the sensory, emotional and functional aspects of the pain experience. This questionnaire has been shown to be reliable and valid in patients with osteoarthritis.^54^ The main criteria will be defined as the score of current perceived pain in the more painful hand with a higher score meaning a higher level of pain (for a psychometric justification of choosing a single-item numerical score as main outcome, see Salaffi *et al*).^55^

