### Intervention

All participants will be provided with a virtual reality headset with an integrated audio system. The Meta Quest Pro, released in 2022, will be used. A tablet connected to the headset will host the hypnosis application developed by Super Splendide (www.supersplendide.com), a company that specialises in the development of virtual reality applications. In collaboration with clinicians, researchers in the field of medical hypnosis and patient partners, Super Splendide is developing an intervention programme that combines VRH. The intervention will be delivered by one of the team members (research assistant adequately trained to communicate with participants, the intervention and the measurement tools) and supervised by VF (postdoctoral researcher in health psychology) and DO (senior researcher and clinical psychologist in pain clinics). Supervisors will be in charge of verifying the correct running of recruitments and data collection and will check those points once every 2 weeks.

For sessions 1 and 2 (ie, time 1 and time 2), participants from both the experimental and control group will not interact with the environment; they will simply be asked to watch and explore a 3D animation of a beach or a forest and relax during the session. The sounds may include the ocean, birds, wind, a crackling campfire and relaxing music. In the control group, sessions 3 and 4 (ie, time 3 and time 4) will consist of the repetition of sessions 1 and 2. In the experimental group, participants will be introduced to hypnosis techniques, the ‘magic hand’ intervention (ie, learning to apply analgesia with their hand) and to an intervention that involves manipulating their pain through an augmented reality script.

A counterbalancing procedure will be applied, respectively for sessions 1 and 2 (ie, beach or forest) and for sessions 3 and 4 (ie, magic hand or pain manipulation).

The fifth session (ie, time 5, follow-up) will correspond to a repetition of the first session (ie, time 1), the aim being to collect data in the exact same conditions to compare baseline and data collected after the intervention.

Given that cybersickness (ie, symptoms occurring when people are exposed to virtual reality) could occur, this variable will be systematically controlled for after each session in all participants with a dedicated questionnaire.^61^

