### Data collection

Consent, questionnaire data and sociodemographic information will be provided by participants on a tablet using the software REDCap. The tablet will be provided by the research assistant in charge of data collection.

Participants will be included prospectively over a 6-week period. Participants will be received five times: the first four sessions (ie, time 1, time 2, time 3, time 4) occurring at a week’s interval, and a fifth session, corresponding to a follow-up session, occurring 3 weeks after the fourth session (ie, repetition of the first session).

After providing their informed consent, participants will be assigned to the previously randomly determined group (ie, the experimental group receiving the intervention or the control group) using the online tool Research Randomizer.^62^ All participants will be asked to avoid caffeinated beverages within 4 hours before the study, to avoid smoking 2 hours before the study and to avoid consuming any stimulants in general.

Participants will be received at Maisonneuve-Rosemont Hospital (Montreal, Quebec, Canada) and seated in a designated study room. This room provides a controlled, quiet environment with a comfortable seat. Before the first session, participants will complete a sociodemographic and clinical questionnaire. Participants will answer questionnaires assessing subjective variables of interest before and after each session (ie, time 1, time 2, time 3, time 4 and time 5). Physiological measurements will be taken from 10 min before the beginning of the intervention.

Figure 1 displays a schematic representation of the procedure.

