## Discussion

Chronic pain is a frequent and burdensome condition, with a prevalence that is expected to increase over the following decades because of the ageing population.^6 9^ Treatment of this condition remains lacunary, which appeals for the development of cost-effective solutions that do not require the constant presence of working professionals.^10^ In that sense, this study is particularly original as it explores the therapeutic potential of an emerging technology in a way that has not been extensively studied before. Its aim is to evaluate the effectiveness of a VRH intervention in reducing chronic pain among patients who are particularly vulnerable to this condition and prone to therapeutical wandering. Given the limited research on VRH and its methodological constraints (ie, small sample sizes, no control group, focused on acute pain, absence of a solid methodology of intervention development), the current study prioritises addressing these concerns and implements a longitudinal model that allows for a more comprehensive assessment of the effects of VRH on chronic pain relief. Because of its non-invasive and non-pharmacological nature, VRH holds great clinical and practical potential for chronic pain management. By being accessible in various settings, such as home-based care, hospitals and elderly care facilities, this accessible medication-free alternative treatment, that does not require continuous professional supervision, could enhance patient autonomy and facilitate broader access to pain management solutions. By advancing knowledge in this field, the findings could contribute to the development of innovative patient-centred approaches to treat chronic pain. Additionally, this research paves the way for future investigations into the long-term effects of VRH and its applicability to various types of chronic pain conditions.

One of the major limitations of this study could be the modalities of intervention itself. Indeed, literature suggests that virtual reality is effective on pain control. In that sense, all participants will benefit from an effective intervention given both experimental and control groups will have virtual reality material. In that sense, a major risk of this study is to observe only a floor effect on the different variables. Moreover, given those elements, no placebo condition is expected given no placebo VR intervention seems to be available.

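### The added within-arm hypothesis could be significant with no hypnosis effect, and the between-arm comparison that should carry the conclusion is not tied to one contrast

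*Protocol article*

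**What the plan says.** The Objectives section states how the main aim is met: "This will be achieved by comparing an experimental group, receiving the VRH treatment, to an active control group". It expects lower pain in the VRH arm than in the control arm and gives no time point. It then adds that "pain scores of individuals who received the VRH intervention will show a significant reduction in pain perception between the first and last treatment session", and that this reduction will persist three weeks after the final session.

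Other sections bear on the same comparison:

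- **Primary outcome:** "The main criteria will be defined as the score of current perceived pain in the more painful hand". No time point is given.
- **Abstract, Methods and analysis:** "The effectiveness of the intervention on current perceived pain before and after the intervention (primary outcome) will be evaluated".
- **Intervention:** sessions 1 and 2 are VR without hypnosis in both arms. Hypnosis enters the experimental arm in sessions 3 and 4. Time 5 repeats session 1, "the aim being to collect data in the exact same conditions to compare baseline and data collected after the intervention".
- **Data collection:** "Participants will answer questionnaires assessing subjective variables of interest before and after each session". Five sessions give up to ten pain scores per patient.
- **Power analysis and statistical analysis:** the sample size of 82 comes from a repeated-measures analysis of variance with a between-group factor, f = 0.25, at two-sided 0.05. The analysis model is left to depend on the structure of the data.
- **Discussion:** "all participants will benefit from an effective intervention given both experimental and control groups will have virtual reality material".

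**The concern.** The only randomised question is what hypnosis adds to VR. A before-to-after change inside the VRH arm mixes any hypnosis effect with the effect of VR, the passage of time and regression to the mean. The Discussion makes such a shared improvement the expected case. A significant fall in that arm could therefore be reported under the main objective although the control arm improved just as much.

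The claim of stability has the opposite weakness. It is also a within-arm statement, and failing to find a significant change from time 4 to time 5 would appear to confirm it, even where the study simply could not detect a loss of benefit.

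The between-arm comparison should carry the conclusion, but it could mean the level or change at the end of treatment, at follow-up, or averaged over sessions, using pre-session or post-session scores. These answer different questions and have different power.

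**Working it through.** **Inputs.** From the protocol: n = 82, f = 0.25 (d = 0.5 for two groups), alpha 0.05 two-sided, target power 0.80. Assumed because the protocol gives no figure: 41 per arm, the number of measurements m, the correlation between scores (r or rho), and the size of any improvement shared by both arms.

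**1. The plan's own figure.** For a repeated-measures between-group factor, lambda = f² × N × m / (1 + (m − 1) × rho), with df (1, N − 2). With m = 4 and rho = 0.5, lambda = 0.0625 × 82 × 4 / 2.5 = 8.2. Power is 0.808, and 82 is the smallest even N reaching 0.80. So 82 fits a group difference averaged over about four occasions. It does not belong to a within-arm test or a single-time comparison.

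**2. Within-arm test with zero hypnosis effect.** This is a paired t test with n = 41. The standardised change is dz = shared change / √(2(1 − r)), with the shared change in SDs of the score, and the noncentrality is dz × √41.

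| Shared change (SD) | r = 0.5 | r = 0.7 |
|---|---|---|
| 0 | 5% | 5% |
| 0.3 | dz 0.30: 47% | dz 0.39: 68% |
| 0.5 | dz 0.50: 88% | dz 0.65: 98% |

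A simulation of 20,000 trials at r = 0.5 gave 47% and 87% for shared changes of 0.3 and 0.5 SD. The between-arm test of change in the same simulated trials stayed at 5%.

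**3. Stability.** The same calculation run the other way: if 0.3 SD of the benefit were truly lost by time 5, the paired test would be non-significant in 100 − 47 = 53% of trials at r = 0.5, and in 100 − 68 = 32% at r = 0.7. Non-significance is weak evidence of persistence.

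**4. A single between-arm contrast with 82 analysed, d = 0.5.** Unadjusted, the noncentrality is 0.5 × √(41/2) = 2.26, which gives 61% power. With ANCOVA the effective d is 0.5 / √(1 − rho²):

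| rho with baseline | Effective d | Power |
|---|---|---|
| 0.3 | 0.524 | 65% |
| 0.5 | 0.577 | 73% |
| 0.7 | 0.700 | 88% |

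For 80% power, the number analysed would be 128 unadjusted, or 98 by ANCOVA at rho = 0.5.

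**5. The averaged contrast.** The arms are treated alike in sessions 1 and 2. If they differ by f = 0.25 only at times 3 and 4, the group effect averaged over times 1 to 4 is f = 0.125. Then lambda = 0.015625 × 82 × 4 / 2.5 = 2.05, and power is 29%. If they differ at times 3 to 5, the effect averaged over times 1 to 5 is f = 0.15, lambda = 0.0225 × 82 × 5 / 3 = 3.08, and power is 41%. The choice of contrast therefore matters for the sample size as well as for interpretation.

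**The case against.** The strongest reply is that the protocol already has a between-arm primary comparison. The Objectives say the aim is met by comparing the arms, and the sample size rests on a between-group factor. The within-arm sentence is plainly additive: "It is also expected that pain scores of individuals who received the VRH intervention will show a significant reduction in pain perception". This stands.

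A reader might infer that the primary comparison is defined in three incompatible ways. The documents do not support that. The abstract's wording fits a between-arm comparison, and the Intervention section only explains why session 5 repeats session 1. These statements are unspecific; they are not rival definitions.

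A reader might also infer an inflated error rate from choosing among contrasts. Picking the best of three plausible between-arm contrasts would give a false-positive rate of about 13%, but no section plans such a selection and those three contrasts are not listed anywhere in the protocol.

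It can further be said that a condensed article may leave the exact time point to a fuller document, and that the trial is a phase II study of feasibility and preliminary efficacy. An unnamed time point alone would indeed be a minor matter. But the within-arm hypothesis is stated in this article, under the main objective and in terms of significance. The closing discussion also speaks of demonstrating effectiveness and efficacy, so the pilot label does not remove the problem.

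**Conclusion.** The concern holds in a limited form and should be fixed. The within-arm expectation is an additional hypothesis. No section makes it the primary test or says that meeting it counts as success. It nevertheless cannot separate hypnosis from VR, and it could be significant with no hypnosis effect: 5% with no shared change, 47% to 98% for a shared change of 0.3 to 0.5 SD. That range assumes 41 patients in the arm and r of 0.5 to 0.7; the protocol gives no figure for the shared change or the correlation, so the result is a possibility and not a prediction. The linked stability claim cannot be established by a non-significant change.

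The between-arm comparison needs one stated contrast, because power at 82 analysed differs widely between the readings: about 81% for the averaged effect as apparently planned, 61% to 88% for a single time point, and 29% to 41% for an averaged effect that includes the sessions without hypnosis.

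**What to change.** - Base every efficacy conclusion, including durability at time 5, on the between-arm difference in current pain adjusted for pre-session time-1 pain, with its confidence interval.
- Report within-arm change descriptively, without a significance claim. Replace the stability expectation with the adjusted between-arm difference at time 5.
- Name one post-hypnosis time point as primary, and say whether the pre-session or post-session score is used. The end of treatment at time 4 and the follow-up at time 5 are both defensible. The investigators should choose before any unblinded analysis and make the other the key secondary.
- Use the same wording in the abstract, Objectives, Intervention and statistical sections, and in the registrations.
- Restate the power for the chosen contrast, giving the assumed correlation with baseline.

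No new assessments are needed. The cost is a change of wording, a stated power that may be less favourable than 80%, and the other time points becoming secondary or descriptive.
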